### Endpoints and assessments

2.3

The co-primary endpoints are dose reductions due to toxicity and PFS, defined as the time from randomisation until the date of either objective radiological disease progression or combined biochemical and clinical progression or death. The reasons for dose reductions will be recorded. Objective radiological disease progression will be assessed according to the Response Evaluation Criteria in Solid Tumours (RECIST) version 1.1, or modified RECIST according to the Gynecologic Cancer Intergroup (GCIG) if there is no measurable disease at baseline [22,23]. Biochemical progression is assessed according to the GCIG criteria for CA-125 and clinical progression will be established by the treating physician [23].

For toxicity, adverse events will be scored according to the Common Terminology Criteria for Adverse Events (CTCAE) version 5.0 [24]. Patient health status and quality of life will be measured with the EuroQol 5 dimensions 5 levels questionnaire (EQ-5D-5L) version 1.1 [25]. Patient satisfaction in terms of cancer therapy will be assessed with the Cancer Therapy Satisfaction Questionnaire (CTSQ) [26]. To measure costs from the societal perspective for the cost-effectiveness analysis, the Institute for Medical Technology Assessment (iMTA) Productivity Cost Questionnaire (iPCQ) and iMTA Medical Consumption Questionnaire (iMCQ) will be used [27,28]. ctDNA levels in plasma will be measured with shallow Whole Genome Sequencing (sWGS) and/or a hybrid-capture based Next Generation Sequencing (NGS) panel, dependent on the most recent insights at time of analysis. ctDNA levels will be corrected for germline and clonal haematopoietic variants with matched peripheral blood mononuclear cells. Olaparib plasma concentrations will be measured by cross-validated liquid chromatography tandem mass-spectrometry assays [21,29,30]. Intratumoral olaparib concentrations will be assessed from optional tumour biopsies. The frequency of the above-mentioned assessments is outlined in Table 2.

**Table 2 tbl2:** Overview of measurements in PROACTIVE-B study.

	Baseline	Week 4	Week 6	Week 8	Week 12	Every 3 months	Every 6 months	At progression
Clinical evaluation	X	X		X	X	X	X	
Laboratory	X	X		X	X	X	X	
Adverse events	X	X		X	X			
Radiological evaluation	X				X		X	
ctDNA	X	X		X	X			X
Plasma olaparib PK		X		X	X			
Intratumoral olaparib PK				X				X
Online questionnaires	EQ-5D-5L iPCQ iMCQ		CTSQ EQ-5D-5L iPCQ		CTSQ EQ-5D-5L iPCQ iMCQ		CTSQ EQ-5D-5L iPCQ iMCQ	EQ-5D-5L

ctDNA: circulating tumour DNA; CTSQ: Cancer Therapy Satisfaction Questionnaire; EQ-5D-5L: EuroQol 5 dimensions 5 levels questionnaire; iMCQ: iMTA Medical Consumption Questionnaire; iPCQ: iMTA Productivity Cost Question.

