We propose pharmacokinetic (PK) boosting to reduce the dose of expensive anticancer drugs while improving the safety profile and maintaining efficacy for our patients. PK boosting is the lay term for administering a non-therapeutic active strong inhibitor of a metabolic enzyme, for example cytochrome P450 3A (CYP3A), together with a therapeutic drug that is metabolized by the same enzyme. For the treatment of Human Immunodeficiency Virus (HIV)-infection, PK boosting is routinely used in millions of people worldwide for over two decades and can, therefore, be considered as a feasible and safe approach to implement in practice [13,14]. Since many oral targeted oncolytic drugs are metabolized by CYP3A iso-enzymes, boosting could be a valuable tool to reduce the dose and, thereby, costs for many more anticancer drugs [15]. PK boosting will increase the bioavailability, due to pre-systemic CYP3A-inhibition, and decrease the elimination, due to systemic CYP3A-inhibition, of drugs that are substrates of this enzyme [13]. Therefore, the dose of a boosted drug may be reduced without compromising effective exposure. Additionally, inhibition of CYP3A could lead to less PK variability since metabolic capacity is a prominent cause for variability in systemic exposure [14]. Olaparib shows a wide variability in plasma concentrations which might be reduced by CYP3A-inhibition [16]. Predictable olaparib exposure will reduce the number of patients who are either unintentionally undertreated, or overtreated, which bears the potential to reduce suboptimal responses and reduce toxicity related to high exposure [17]. Moreover, intratumoral overexpression of CYP3A has been reported as a possible detoxification or resistance mechanism in many different types of cancer, including breast and ovarian cancer compared to healthy tissue [18,19]. Theoretically, inhibition of CYP3A by the “booster agent” may lead to higher intratumoral concentrations of the drug and may subsequently result in a more effective PARP-inhibition in tumour cells [20].

Recently, the proof-of-concept PROACTIVE-A study has shown that PK boosting of olaparib is feasible. The boosted therapy of olaparib 100 mg twice daily (BID) with the potent CYP3A-inhibitor cobicistat 150 mg BID increased olaparib exposure 1.45-fold compared to the standard therapy of olaparib 300 mg BID [21]. In PROACTIVE-A, patients received the boosted therapy for one week, precluding conclusions on efficacy and longer-term tolerability.

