### Design

2.1

PROACTIVE-B is a Dutch nationwide, open-label, randomised, multicentre trial comparing boosted olaparib therapy with standard dose olaparib monotherapy in patients with solid tumours (Fig. 1). Patients will be randomised 1:1 between standard olaparib monotherapy and the boosted therapy of olaparib and cobicistat by a variable block randomisation. Randomisation will be stratified by tumour type (BRCA-mutated, high-grade, serous ovarian cancer treated with olaparib after first-line platinum-based chemotherapy, or other) and response to chemotherapy (i.e., complete, or partial response). The standard full dose of olaparib monotherapy consists of 300 mg BID. The boosted full dose of olaparib consists of 100 mg BID with cobicistat 150 mg BID. Dose reductions will be performed according to Table 1, in line with the drug label and the physician's discretion. Patients will visit the outpatient clinic at baseline, after 4, 8, 12 weeks and thereafter every three months until progression or the end of olaparib therapy, in line with standard clinical care. Patients will continue treatment until they do not longer experience clinical benefit or until the end of treatment according to the drug label and/or treatment guideline. This current protocol is approved by the Medical Research Ethics Committee Oost-Nederland and is conducted in accordance with Good Clinical Practice and the Declaration of Helsinki.

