**Fig. 1 fig1:**
[figure not shown]
Study design of the PROACTIVE-B study. BRCA: Breast Cancer gene; CYP3A: Cytochrome P450 3A enzymes; ECOG: Eastern Cooperative Oncology Group; PK: Pharmacokinetics; PFS: Progression-free survival.

**Table 1 tbl1:** Olaparib monotherapy and boosted therapy dose levels.

	Standard monotherapy		Boosted therapy		
	Olaparib	Dose density	Olaparib	Cobicistat	Dose density
**Standard dose**	300 mg BID	100 %	100 mg BID	150 mg BID	100 %
**1st dose reduction**	250 mg BID	83 %	150 mg OD	150 mg BID	75 %
**2nd dose reduction**	200 mg BID	67 %	100 mg OD	150 mg BID	50 %

BID: twice daily; OD: once daily.

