### Objectives

2.2

The primary objective of this study is to determine if boosted olaparib therapy is non-inferior to standard monotherapy concerning both tolerability and efficacy. Tolerability will be measured by dose reductions due to toxicity. Efficacy will be measured by progression-free survival (PFS) in patients with high-grade serous BRCA-mutated ovarian cancer treated with olaparib maintenance therapy after first-line platinum-based chemotherapy.

Secondary objectives include establishing potential differences in type of toxicity, patient health status, therapy satisfaction, cost-effectiveness between treatment arms. Moreover, the predictive value of circulating tumour DNA (ctDNA) as a pharmacodynamic response marker will be evaluated. Exploratory objectives include the association between olaparib PK and toxicity and efficacy, and the association between patient characteristics and olaparib PK and efficacy. Finally, differences in intratumoral olaparib concentrations between treatment arms will be explored.

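### Table 2 schedules adverse event grading only to week 12, so later non-laboratory toxicity that leads to no dose reduction has no scheduled grading, although tolerability is judged at twelve months

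*Protocol article*

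**What the plan says.** All references are to the protocol article.

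- **Endpoint and horizon.** Section 2.2 measures tolerability by dose reductions due to toxicity. Section 2.7 compares the proportions at twelve months.
- **Who decides a reduction.** The trial is open-label. Section 2.1 states: "Dose reductions will be performed according to Table 1, in line with the drug label and the physician's discretion". Section 2.3 adds: "The reasons for dose reductions will be recorded".
- **Grading.** Section 2.3 scores adverse events by CTCAE version 5.0 and refers to Table 2 for timing: "The frequency of the above-mentioned assessments is outlined in Table 2".
- **Table 2.** The adverse events row is marked at baseline and weeks 4, 8 and 12. It is blank under the three-monthly, six-monthly and progression columns. The clinical evaluation and laboratory rows are marked under both recurring columns.
- **Visits.** After week 12, section 2.1 has patients seen "thereafter every three months until progression or the end of olaparib therapy, in line with standard clinical care".
- **Why toxicity matters here.** Section 1 says of the preceding study: "In PROACTIVE-A, patients received the boosted therapy for one week, precluding conclusions on efficacy and longer-term tolerability". Section 2.2 adds: "Secondary objectives include establishing potential differences in type of toxicity, patient health status, therapy satisfaction, cost-effectiveness between treatment arms".
- **Planned analysis.** Section 2.7 describes adverse events with descriptive statistics and states no time horizon.

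**The concern.** A dose reduction is a decision as well as an outcome. In an open-label trial, two arms can show similar reduction counts while patients in one of them put up with more symptoms at full dose. Graded adverse events are the direct check on that.

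The question is a live one. Section 1 reports a 1.45-fold rise in olaparib exposure with boosting in the preceding study, and section 3 says higher exposure may bring more adverse events.

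If Table 2 is followed as printed, that check is systematic for the first 12 weeks only. Two things are at stake: the secondary comparison of type of toxicity, and the confidence with which a twelve-month reduction count can be read as longer-term tolerability. An analysis plan written later cannot recover grades that were never collected.

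**Working it through.** **1. The plan's own figure.** The only calculation near this point is the tolerability sample size in section 2.6: 28% in each group, margin 24 points, type I error 0.01, power 80%. With one-sided 0.01 and unpooled variance,

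n = (2.326 + 0.842)² × 2 × 0.28 × 0.72 / 0.24² = 10.04 × 7.0 = 70.3, which rounds up to 71 per group.

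This is the stated figure. The point disputes no number in the plan, and its fix does not change the sample size.

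**2. Scheduled visits against scheduled grading.** Week 12 is taken as month 3, and later visits as months 6, 9 and 12.

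| Post-baseline visit | Clinical and laboratory | Adverse events |
|---|---|---|
| Week 4 | marked | marked |
| Week 8 | marked | marked |
| Week 12 | marked | marked |
| Months 6, 9, 12 | marked | blank |

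Adverse events are marked at 3 of 6 post-baseline visits. In calendar time, 52 − 12 = 40 of 52 weeks (77%) lie beyond the last mark. The two rows above are marked in the recurring columns, so the blank cells are unlikely to be a fault of text extraction.

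**3. What is still collected after week 12.**

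- Dose reductions and their reasons, with no time limit stated. Toxicity that leads to a reduction is therefore captured.
- Three-monthly laboratory tests. Anaemia can be graded from these if the panel includes a blood count; Table 2 does not itemise it.
- Six-monthly questionnaires ("CTSQ EQ-5D-5L iPCQ iMCQ"). These cover health status, satisfaction and costs, and none is a CTCAE grade.
- Adverse events at extra visits outside the protocol (section 3). These are unscheduled, so their frequency may differ between arms.

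What remains without scheduled grading is non-laboratory toxicity after week 12 that does not lead to a reduction. Gastro-intestinal symptoms are the main example: section 2.6 names them, with anaemia, as the most prominent adverse events.

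**4. Size of the remedy.** The upper limit is 3 × 142 = 426 added assessments. If visits stop at progression, 88% are progression-free at twelve months (section 2.6, applied here to all 142 patients) and the hazard is constant:

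142 × (0.88^0.5 + 0.88^0.75 + 0.88) = 142 × (0.938 + 0.909 + 0.880) ≈ 387.

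Patients who stop olaparib earlier would lower this further.

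**The case against.** **The type-of-toxicity objective has no stated horizon and its analysis is descriptive, so grading to week 12 can serve it.** This stands in part. No sentence is contradicted outright. But the objective is not limited to 12 weeks either, and a reader would take it to cover the same year as the tolerability endpoint.

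**Toxicity comes early.** Section 2.6 says patients are watched closely at first and that the main adverse events usually appear soon after the start. This stands as a limit on size: 40 of 52 weeks is calendar time, not a share of the toxicity. It does not settle the matter, because the plan uses the argument to support a wide margin rather than to end grading, and symptoms that begin early can persist.

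**It may be only a labelling gap in a condensed article.** Section 3's remark that extra visits are also monitored for adverse events can be read as implying that every protocol visit reports them, and the full protocol is not at hand. This may be so. In that case the Table 2 row is wrong, since section 2.3 makes that table the source for frequency. Either reading calls for a change to the row.

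**Stronger inferences.** A reader might infer that the tolerability co-primary cannot be ascertained after week 12, or that no toxicity data exist after that point. The documents support neither: reductions and their reasons are recorded, visits continue, and laboratory tests continue.

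**Conclusion.** The concern holds in a limited form. As printed, Table 2 ends scheduled CTCAE grading at week 12, while visits and the tolerability endpoint run to twelve months. The loss is confined to later non-laboratory toxicity that does not lead to a dose reduction. It weakens the secondary comparison of type of toxicity and the interpretation of the reduction count. It does not affect the co-primary test, its margin, its error rate or the sample size.

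The measurable size is 3 of 6 post-baseline visits unmarked. How much toxicity falls in that window cannot be derived from the document, and the plan expects most of it earlier.

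A reader might also look at Table 1 ("Olaparib monotherapy and boosted therapy dose levels"), where the first step goes to 83% of full dose in one arm and 75% in the other, and infer that the reduction count is biased. The document gives no direction or size for such an effect, and it does not depend on the adverse event schedule. It forms no part of this point.

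The conclusion rests on reading the blank cells as intended. If adverse events are in fact graded at every visit, the point reduces to correcting one table row.

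**What to change.** 1. **Table 2.** Mark adverse events at the existing three-monthly visits up to month 12. If they are already graded there, correct the row to show it.
2. **Section 2.7.** Describe CTCAE events by arm, type and grade to month 12. Include gastro-intestinal symptoms of grade 2 or higher as well as all events of grade 3 or higher. A summary of grade 3 or higher alone would miss the lower-grade symptoms most likely to be tolerated at full dose. State that this is for interpretation only, with no decision rule.
3. **If collection cannot be extended.** State that the graded-toxicity comparison covers the first 12 weeks.

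The co-primary test, its margin and Table 1 stay as they are.

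**Cost.** At most 426 further assessments, or about 387 under the assumptions above, all at visits that already include clinical evaluation and laboratory tests. The trial is ongoing, so patients already past week 12 would need chart review, where symptom grading is less reliable. Grading remains unblinded.

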### Study population

2.4

Patients are eligible for this study when the following inclusion criteria are met.•Age ≥18 year;•Starting with olaparib treatment, according to the drug label and physician's discretion;•Expected to be on olaparib treatment for ≥3 months;•Eastern Cooperative Oncology Group (ECOG) performance status of 0–3;•Able and willing to provide written informed consent prior to screening;•Able to measure the outcome of the study in this patient (e.g., patient availability; willing and being able to undergo sample collection).

Patients will be excluded if any of the following exclusion criteria apply.•Concurrent use of other anticancer therapies;•Concurrent use of potent inducers or inhibitors of CYP3A4 as assessed with the Dutch database *KNMP G-standard;*•Known contra-indications for cobicistat according to the Summary of Product Characteristics (e.g., concomitant use of alfuzosin, carbamazepine, phenytoin, colchicine, rifampin).

In total, 128 of the 142 patients should receive olaparib as maintenance therapy for BRCA-mutated, FIGO III/IV ovarian cancer after response on first-line platinum-containing chemotherapy for the evaluation of efficacy in a homogenous population. The remaining 14 patients should receive olaparib for any approved indication of olaparib according to the drug label, to illustrate the extrapolation of the boosting concept in other populations. These 14 patients are pooled with the 128 patients with ovarian cancer for the evaluation of tolerability as the incidence of dose reductions due to adverse reactions is theoretically similar across tumour types [4,[31], [32], [33], [34]].

Patients may decide to withdraw from the study at any time. Patients without an event, who withdraw within three months after start will be replaced by a new eligible patient. Replaced patients will be monitored to prevent bias, a maximum of ∼30 % can be replaced.

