### Statistical analysis

2.7

An intention-to-treat, and per protocol, analysis will be performed in line with guidelines. The per-protocol analysis will be leading, but it is not expected that cross-over will take place. Proportions of patients with dose reductions due to toxicity at twelve months will be compared between both treatment arms with the Chi-square test for proportions. Additionally, a Kaplan-Meier approach will be used to compare PFS rates between both treatment arms in the efficacy population.

Linear mixed-effects models will be used to evaluate differences in patient health status and therapy satisfaction over time and between treatment arms. Descriptive statistics will be used to describe adverse events and intratumoral olaparib concentration. The association between ctDNA levels and clinical outcomes (PFS/OS) will be explored with a Cox proportional hazard model with a correction for previously defined prognostic factors [37]. Additionally, cost-effectiveness will be analysed in line with the most recent guideline for economical evaluations in healthcare by the Dutch Healthcare Institute [38]. In line with this guideline, we will adopt a societal perspective and a life time horizon to calculate the costs per quality adjusted life year (QALY) in a cost-utility analysis [38].

The patterns and extend of missing data over time and between treatment arms will be explored. As the primary endpoints are easy to assess, missing data is expected to be minimal for the primary analysis. In case of unexpected high proportions of missing data or missing data that can be classified as Missing Not At Random (MNAR), imputation methods and/or sensitivity analyses will be applied [39].

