To ensure feasibility of the protocol, this study is aligned with the current standard clinical practice as much as possible. Additional follow-up visits outside the study protocol are accepted and monitored for adverse event reporting as well. Questionnaires will be sent out online to reduce burden for the clinic and research staff, but also to make it as convenient as possible for patients who can fill in the questionnaires at a moment that fits them best.

The wide inclusion criteria of the study will result in a study population that reflects the real-world population. This will lead to broad external validity of our results. Of note, there is no exclusion criterion for patients treated with comedication that are substrates for CYP3A. These drugs could also be affected by cobicistat and, therefore, patients are screened for drug-drug interactions through routine workflows. Relevant interactions may limit the use of cobicistat. Due to the extensive experience with these drugs in antiretroviral therapy, this is considered a manageable hurdle [40].

Besides the clinical evaluation of the boosted therapy, this study incorporates several emerging research topics. In the past years, ctDNA analysis have provided valuable insights in its clinical validity in several cancer types [41]. In patients with ovarian cancer, ctDNA is correlated with the volume of disease and holds promise as a biomarker for disease monitoring [42,43]. This is interesting, considering the poor concordance between CA-125 and radiological progression in patients treated with PARP-inhibitors [44]. Moreover, reversion mutations could be detected in ctDNA of patients after treatment with olaparib and cediranib, which could provide valuable insights for treatment optimization [45].

Also, tumour biopsies will shed light on the intratumoral olaparib concentration, which might be increased with the boosted therapy and could therefore be a potential tool to convert resistance. Preclinical studies have shown that tumours are able to express CYP3A as a detoxification mechanism [18,20]. By inhibiting CYP3A, PK boosting might even increase intratumoral olaparib concentrations by CYP3A-inhibition and could therefore improve efficacy. The tumour biopsies are optional in this study, but even a small number of biopsies will provide new insights.

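### Replacing early leavers without an event, with the per-protocol analysis leading, can bias tolerability toward non-inferiority if toxicity-related withdrawal is more frequent on the boosted arm

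*Protocol article*

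**What the plan says.** Under Study population (2.4): "Patients without an event, who withdraw within three months after start will be replaced by a new eligible patient". The next sentence gives the limit and the safeguard: "Replaced patients will be monitored to prevent bias, a maximum of ∼30 % can be replaced". The article does not define the event, the denominator of the 30%, or what the monitoring does.

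Under Statistical analysis (2.7): "An intention-to-treat, and per protocol, analysis will be performed in line with guidelines". Of the two, one is given priority: "The per-protocol analysis will be leading, but it is not expected that cross-over will take place". The tolerability comparison is specified as follows: "Proportions of patients with dose reductions due to toxicity at twelve months will be compared between both treatment arms". Withdrawal or discontinuation because of toxicity is not named as part of this endpoint, either here or under Endpoints and assessments (2.3).

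The Design section (2.1) begins: "PROACTIVE-B is a Dutch nationwide, open-label, randomised, multicentre trial".

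**The concern.** The replacement rule acts after randomisation and depends on outcome. An early leaver with an event is kept, and one without is exchanged for a new patient. Because the trial is open-label, the decision to leave can depend on knowing the arm.

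What matters is which patients count as event-free. If the tolerability event is a dose reduction due to toxicity and nothing else, someone who leaves the study for toxicity before any reduction is event-free. That patient tolerated treatment badly, yet is substituted by someone whose later result takes the place.

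The article itself makes a difference between arms plausible. Section 2.6 expects the main adverse events to appear soon after start, which is likely to overlap the three-month window. The Background reports 1.45-fold olaparib exposure with boosting in PROACTIVE-A, and the Discussion accepts that higher exposure may bring more adverse events. At stake is the 1% type I error assigned to tolerability.

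**Working it through.** **Inputs from section 2.6.** Tolerability: margin 0.24, type I error 0.01, power 80%, 28% reductions in each arm, 71 per arm. Efficacy: margin 0.15, type I error 0.04, power 80%, 88% progression-free at 12 months, 64 per arm.

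**The plan's own figures.** With n = (z₁₋α + z₀.₈₀)² × 2p(1−p) / margin² and one-sided α:

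- Tolerability: (2.326 + 0.842)² × 2 × 0.28 × 0.72 / 0.24² = 10.04 × 0.4032 / 0.0576 = 70.3, so 71 per arm.
- Efficacy: (1.751 + 0.842)² × 2 × 0.88 × 0.12 / 0.15² = 6.72 × 0.2112 / 0.0225 = 63.1, so 64 per arm.

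Both match. Two-sided α would give 82 and 79, so the stated errors are one-sided.

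**Assumptions for the bias calculation.** Intolerance means a dose reduction due to toxicity, or early withdrawal for toxicity before any reduction. True intolerance is 28% on standard and 52% on boosted, so the true gap equals the margin and a correct test passes 1% of the time. A share w of boosted patients leaves early for toxicity without a reduction. They are replaced in the same arm, so 71 per arm are analysed.

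**Formulae.** Observed boosted rate = (0.52 − w)/(1 − w). With d the observed difference and SE = √[(0.28×0.72 + p_b(1−p_b))/71], P(conclude non-inferiority) = Φ[(0.24 − d)/SE − 2.326].

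Worked case, w = 10%: p_b = 0.42/0.90 = 0.467; d = 0.187; SE = √[(0.2016 + 0.2489)/71] = 0.0797; Φ(0.670 − 2.326) = Φ(−1.657) = 4.9%.

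| w (boosted) | Observed boosted rate | Difference | False non-inferiority | Simulation (400,000 runs) |
|---|---|---|---|---|
| 0% | 52.0% | 24.0 points | 1.0% | 0.9% |
| 5% | 49.5% | 21.5 | 2.2% | 2.1% |
| 10% | 46.7% | 18.7 | 4.9% | 4.6% |
| 15% | 43.5% | 15.5 | 10.4% | 10.0% |
| 20% | 40.0% | 12.0 | 21% | 20.8% |

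The number replaced is 71 × w/(1−w): about 8 patients at w = 10% and 18 at w = 20%. The cap is about 43 if taken of 142 (0.30 × 142 = 42.6) and about 21 if taken of 71 per arm (21.3), so both cases fit under either reading.

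**When both arms lose patients to toxicity.** The same formula is applied to each arm:

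- 5% standard, 15% boosted: 24.2% vs 43.5%, error 4.2%.
- 10% standard, 20% boosted: 20.0% vs 40.0%, error 3.7%.
- 5% in each: 24.2% vs 49.5%, error 0.6%.
- 10% in each: 20.0% vs 46.7%, error 0.4%.

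Inflation therefore needs more toxicity-related withdrawal on the boosted arm.

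**Does ending replacement suffice?** Suppose 5% of standard and 20% of boosted patients leave for toxicity without a reduction, and 28% of the rest have reductions.

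- Leavers replaced: 28% vs 28%, difference 0.
- Leavers kept but scored as non-events: 0.95 × 0.28 = 26.6% vs 0.80 × 0.28 = 22.4%, so boosted looks 4.2 points better.
- Leavers kept and counted as events: 0.05 + 0.266 = 31.6% vs 0.20 + 0.224 = 42.4%, difference 10.8 points.

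Retention alone makes the masking worse; how leavers are scored has to change too. This example shows direction only: 10.8 points is inside the margin, so concluding non-inferiority there would be correct.

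**The case against.** Several points against the concern have force.

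- The article also says early adverse events are readily handled by reducing the dose. On that premise most early toxicity produces an event, and patients with an event are not replaced. This limits how large w is likely to be, but the rule still covers those who leave first.
- The rule concerns withdrawal from the study. Nothing says that stopping the drug for toxicity counts as study withdrawal, so the text does not show that everyone who stops boosted treatment disappears. The bias comes only from those who leave the study.
- A reader might infer that replacement contradicts the promised intention-to-treat analysis. The article does not say that replaced patients leave that set, and set membership is a detail an article may leave to fuller documents. Still, the intention-to-treat analysis does not lead, and as worded it would score these patients as non-events.
- A reader might infer that any early withdrawal favours boosting. It does not: equal loss leaves the error below 1%, and withdrawal unrelated to outcome does not favour the boosted arm.
- The Discussion's remark that "Relevant interactions may limit the use of cobicistat" might be read as one-arm cross-over after randomisation. The surrounding text describes interaction screening and a manageable problem, and section 2.4 excludes known cobicistat contra-indications. No such cross-over is described.
- Leading with per-protocol while also running intention-to-treat is a recognised non-inferiority convention. Taken alone it would be a preference; here it comes on top of outcome-dependent replacement.

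As for the safeguard, "Replaced patients will be monitored to prevent bias" shows awareness of the problem. Monitoring does not put the substituted patients back into the comparison.

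**Conclusion.** The point holds as a conditional risk to the tolerability conclusion and should be fixed. The stated rules let patients who leave for toxicity before a reduction be exchanged for others, with the leading analysis offering no correction. If this happens more on the boosted arm, the 1% error rises to about 2%, 5% and 21% at 5%, 10% and 20% boosted-arm loss.

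These figures rest on assumed withdrawal rates, a true gap exactly at the margin, same-arm replacement, and reading the undefined event as a dose reduction due to toxicity. If fuller documents already count toxicity withdrawals as events, most of the problem disappears. The calculation does not show that the bias will occur, and it says nothing against the stated sample sizes, which reproduce.

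**What to change.** 1. State that all randomised patients, including those now called replaced, stay in the intention-to-treat set of their assigned arm, followed to month 12 where consent allows. Describe new enrolments as additional.
2. Define the event in the replacement rule. Count withdrawal or discontinuation due to toxicity as a tolerability event in the primary analysis, or at least in a pre-specified sensitivity analysis. Step 1 without this step would leave the boosted arm looking better than it is.
3. Claim non-inferiority only if the intention-to-treat and per-protocol analyses both meet the margin.
4. Report early withdrawals by arm and reason.

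**Cost.** This is mostly wording, and extra enrolment is already allowed. Requiring both sets costs some power. So does a wider endpoint: at an assumed 33% in each arm, SE = √(2 × 0.33 × 0.67/71) = 0.0789, and power is Φ(0.24/0.0789 − 2.326) = Φ(0.715), about 76% instead of 80%. Twelve-month status must be collected for early leavers who agree; some who withdraw will decline. Additional enrolment remains worthwhile: losing 30% of 71 per arm without making it up would cut tolerability power to about 63%.
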